**Objective:**

In this study, we aim to identify the proportion and timing of AF detection and risk stratification criteria in patients with CS in real-world settings in Japan.

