The term “embolic stroke of undetermined source” (ESUS) has been proposed to describe CS that is not lacunar and is not associated with proximal arterial stenosis or a recognizable cardioembolic source [1]. Two international ESUS trials demonstrated that oral anticoagulants (rivaroxaban and dabigatran) were not superior to aspirin for the prevention of recurrent stroke after ESUS [3,4], although a secondary analysis in the RE-SPECT ESUS (Randomized, Double-Blind Evaluation in Secondary Stroke Prevention Comparing the Efficacy and Safety of the Oral Thrombin Inhibitor Dabigatran Etexilate Versus Acetylsalicylic Acid in Patients With Embolic Stroke of Undetermined Source) study demonstrated that, compared with aspirin, dabigatran was associated with a lower risk of recurrent stroke among Japanese patients with ESUS [5]. In Japan, magnetic resonance imaging (MRI) is widely used in the diagnosis of stroke. The Japanese guidelines indicate that MRI is essential in the selection of candidates with CS eligible for ICM implantation [6]. Branch atheromatous disease (BAD) is a single subcortical infarction larger than lacunar stroke in the territories of deep perforators without relevant arterial stenosis [7]. The Japanese guidelines on the clinical indications for ICMs recommend that BAD should not be considered as an indication because it results from a nonembolic mechanism [6]. These procedural differences between Japan and Western countries may impact the detection rate and predictors of AF in patients with CS. However, available data on Japanese patients are limited to small retrospective studies. Furthermore, additional information about AF detection, including the number of episodes, cumulative episode duration, anticoagulation initiation (type and dose of regimen and time of initiation), rate of catheter ablation, role of atrial cardiomyopathy, and stroke recurrence (time of recurrence and cause of the recurrent event), was not provided in the vast majority of previously published studies [8,9].

This study aims to clarify the proportion and timing of AF detection via ICMs in patients diagnosed with CS in Japan. Additionally, we aim to identify risk stratification criteria using real-world data, which could then be used in clinical practice to predict occult AF, identify optimal candidates for ICM implantation, and inform the development of diagnostic criteria.

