### Patient Population

Patient enrollment for this ongoing study started in February 2020 in 24 medical institutions throughout Japan. The inclusion criteria for this study are as follows: (1) patients who have been diagnosed with CS according to the Japanese diagnostic criteria and have been implanted with an ICM (Reveal LINQ), and (2) patients aged 40-90 years. The main exclusion criterion is the presence of contraindications for MRI. A full description of the inclusion and exclusion criteria is presented in Textbox 1.

Inclusion and exclusion criteria.

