### Data Collection

The study data, such as patient background, laboratory data, coagulation test, B-type natriuretic peptide, physiological examination (electrocardiogram [ECG], transthoracic echocardiography, transesophageal echocardiography [TEE], and carotid echocardiography), neuroimaging examination, Mini-Mental State Examination (MMSE), modified Rankin Scale (mRS), and presence of cardiovascular events, gastrointestinal bleeding, and other adverse events, or death (Table 1 and Textbox 2), will be stored on an encrypted website and will be accessible only to study researchers with appropriate training and ethics review board approval. Data monitoring will be performed independently by the study steering committee.

**Table 1 table1:** Overview of study schedule.

Survey items	Baseline survey	6 months (±30 days)	12 months (±30 days)	24 months (±30 days)
Consent withdrawal/visit status/health confirmation		✔	✔	✔
Patient background/history	✔			
Blood count, biochemistry, coagulation test, BNP^a^	✔	✔	✔	✔
Physiological examination (ECG,^b^ TTE,^c^ TEE,^d^ carotid echocardiography)	✔			
Brain MRI^e^ examination	✔	✔	✔	✔
MMSE^f^	✔		✔	✔
mRS^g^	✔	✔	✔	✔
Presence of cardiovascular events, gastrointestinal bleeding, other adverse events, or death		✔	✔	✔

^a^BNP: B-type natriuretic peptide.

^b^ECG: electrocardiogram.

^c^TTE: transthoracic echocardiography.

^d^TEE: transesophageal echocardiography.

^e^MRI: magnetic resonance imaging.

^f^MMSE: Mini-Mental State Examination.

^g^mRS: modified Rankin Scale.

Detailed survey items in this study.

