**Cardiovascular events, gastrointestinal bleeding, cancer, other adverse events, or death**

### Sample Size

Recent retrospective observational ICM studies have demonstrated that major vessel occlusion (n=84) and frequent premature atrial contractions (n=66) were associated with AF detection after adjustment for risk factors and comorbidities, respectively [8,9]. A subanalysis of the CRYSTAL AF (Cryptogenic Stroke and Underlying AF) study (including 221 patients with a 30% AF detection rate) demonstrated that older age and longer PR interval were associated with an increased likelihood of detecting AF [10]. On the basis of the results of these previous studies, we decided to enroll 200 patients in this observational study to perform statistical analyses, including multivariate regression analysis, with sufficient statistical power.

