### Data Analysis Plan

Table 1 presents an overview of the protocol schedule for this study. Categorical variables will be expressed as frequencies and percentages, whereas continuous variables will be expressed as mean with SD or median with IQR, as appropriate. Patient characteristics, medical history, vital signs, laboratory data, the CHA_2_DS_2_-VASc (Congestive Heart Failure, Hypertension, Age [≥75 years], Diabetes, Stroke/Transient Ischemic Attack, Vascular Disease, Age [65-74 years], Sex [Female]) score, neuroimaging characteristics, ECG characteristics, TEE characteristics, MMSE score, mRS score, and stroke recurrence will be compared between patients with AF and patients without AF (Textbox 2). Intergroup differences will be assessed using the chi-square test or the Wilcoxon rank-sum test, as appropriate. The Yates correction or the Fisher exact test will be used if the validity conditions for the chi-square test are not met (theoretical number <5). Furthermore, we will obtain additional information regarding the number of AF episodes, duration of cumulative AF episodes, and time of anticoagulation initiation. We will investigate the rate of initial AF detection within the initial 6, 12, and 24 months after ICM implantation using Kaplan-Meier survival estimates. Cox proportional hazards regression models will be fitted to various baseline characteristics for the prediction of AF. Receiver operating characteristic curve analysis will be performed to assess the predictive accuracy of a variable in AF detection. All analyses will be performed via JMP version 13 (SAS Institute Inc), with *P*<.05 indicating statistical significance.

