## Results

Study recruitment started in February 2020, and thus far, 213 patients have provided written informed consent in May 2021 and are currently in the follow-up phase. The last recruited participant will have completed the 24-month follow-up in May 2023. Data cleanup and analyses are projected to be completed by September 2023, and the results are expected to be submitted for peer-reviewed publication in 2023.

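### Kaplan-Meier is named for a real-world proportion of patients with AF detected; it will overstate that proportion to the extent that patients die before AF is found, probably by a small amount

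*Protocol article*

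**What the plan says.** The target is set out in the Abstract (Objective), where the study is to "identify the proportion and timing of AF detection and risk stratification criteria in patients with CS in real-world settings in Japan", and again in the Introduction: "This study aims to clarify the proportion and timing of AF detection via ICMs in patients diagnosed with CS in Japan". The Discussion also speaks of identifying the proportion of patients with AF.

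The estimator is fixed in the Data Analysis Plan: the "rate of initial AF detection within the initial 6, 12, and 24 months after ICM implantation using Kaplan-Meier survival estimates". No competing-event method is named beside it, and the article does not say how a death before AF detection is handled.

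Three other places bear on how much this matters:
- Patient Population admits "patients aged 40-90 years".
- The exclusion criteria in Textbox 1 remove patients whose illness gives them a life expectancy within two years, which is also the length of follow-up.
- Table 1 in Data Collection lists "Presence of cardiovascular events, gastrointestinal bleeding, other adverse events, or death" as a survey item at 6, 12 and 24 months.

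No mortality figure appears anywhere.

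**The concern.** A patient who dies without AF can never have AF detected. The share of implanted patients in whom AF is found by a given month is therefore a cumulative incidence, with death before AF as a competing event. A standard Kaplan-Meier analysis of time to first AF can only censor such a patient. It then treats the patient as though detection would have continued at the rate seen in those still alive and AF-free.

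The resulting figure answers a different question from the stated aim: how much AF would be found if nobody died. Because the error always goes upward, a larger sample or pooling with other registries would not remove it. What is at stake is the absolute detection figure at 6, 12 and 24 months, which is the first-stated aim of the study.

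**Working it through.** The article states no detection proportion, mortality or power of its own, so there is no planned figure to reproduce. The check compares the two estimands under stated assumptions.

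**Inputs**
- Kaplan-Meier value at 24 months: 30%. The Sample Size section cites a subanalysis "including 221 patients with a 30% AF detection rate" without a time point, so placing it at 24 months is an assumption.
- Mortality m: the 24-month risk of death implied by the death hazard among AF-free patients. It is assumed at 2%, 5% and 10%, because the article gives none.
- Sample size: "we decided to enroll 200 patients in this observational study"; the Results section reports that "213 patients have provided written informed consent".
- Constant, independent hazards of AF detection and death, and no other censoring.

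**Direction.** Let a(s) be the AF detection hazard, A(s) the probability of remaining undetected if nobody died, and G(s) the probability of being alive. Then

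(1 − KM) − CIF = ∫ a(s) A(s) [1 − G(s)] ds ≥ 0.

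This is zero only if no AF-free patient dies before a later detection would have occurred.

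**Size at 24 months.** With cumulative hazards Λ = −ln(0.70) = 0.3567 for AF and D = −ln(1 − m) for death,

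CIF = Λ/(Λ + D) × [1 − 0.70 × (1 − m)].

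- m = 2%: D = 0.0202; 0.3567/0.3769 × 0.3140 = 29.72%
- m = 5%: D = 0.0513; 0.3567/0.4080 × 0.3350 = 29.29%
- m = 10%: D = 0.1054; 0.3567/0.4620 × 0.3700 = 28.56%

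**All three time points** (the same hazards, scaled to 6 and 12 months):

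| Month | 1 − KM | Excess, m = 2% | Excess, m = 5% | Excess, m = 10% |
|---|---|---|---|---|
| 6 | 8.53% | 0.02 | 0.05 | 0.11 |
| 12 | 16.33% | 0.08 | 0.20 | 0.41 |
| 24 | 30.00% | 0.28 | 0.71 | 1.44 |

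Excess is in percentage points. At n = 200, 0.71 points is 0.0071 × 200 ≈ 1.4 patients.

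**Sensitivity**
- Tripling the AF hazard, the death hazard or both in the first 6 months gives a 24-month excess of 0.53 to 0.91 points at m = 5% and 1.06 to 1.83 at m = 10%. The largest 6-month excess in these runs, for m up to 10%, is 0.41 points.
- With a 24-month Kaplan-Meier value of 20% or 40% in place of 30%, the excess at m = 5% is 0.49 or 0.92 points.

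**Against sampling error.** The 95% half-width at 30% is 1.96 × √(0.30 × 0.70/200) = 6.35 points, or 6.15 points at n = 213. The 24-month excess is 0.28/6.35 = 4%, 0.71/6.35 = 11% and 1.44/6.35 = 23% of the half-width at m = 2%, 5% and 10%. Under constant hazards, AF-free mortality would have to reach about 42% over 24 months before the excess equalled the half-width.

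**The case against.** The strongest reply has four parts.

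- **Handling of death is not stated.** The article is a condensed account, and censoring rules are commonly left to a full protocol or SAP. This stands as far as it goes: that deaths are censored is inferred from the method's name. But the article does name the estimator and does name the target. Plain Kaplan-Meier has no other place to put an AF-free death.
- **One minus Kaplan-Meier is a legitimate quantity.** Under independent censoring it estimates detection in the absence of death. That is true, and the choice would be sound if that were the aim. The aim as worded is a real-world proportion.
- **The effect is small and its size is assumed.** This stands. The two-year life-expectancy exclusion acts directly on the competing event. It does not cover unforeseen deaths, so it lowers mortality without removing it.
- **The count of patients with AF will be visible anyway**, because patients with and without AF are compared descriptively. This helps a careful reader, but the 6-, 12- and 24-month figures are the ones tied to Kaplan-Meier.

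A reader might go further and infer that an age limit of 90 implies heavy mortality, or that risk stratification is distorted. The documents support neither inference. They give no mortality and exclude patients expected to die within follow-up. Prediction is planned by Cox regression and ROC analysis, with no Kaplan-Meier estimates by age group. A Cox model that censors deaths validly estimates the cause-specific hazard.

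**Conclusion.** The point holds as a minor mismatch between estimator and aim. If AF-free deaths are censored, as in standard Kaplan-Meier use, the reported proportion will be too high to the extent that patients die before AF is detected. With an assumed 30% at 24 months and assumed mortality of 2% to 10%, the excess is about 0.3 to 1.4 points under constant hazards, and up to about 1.8 points if deaths cluster early. At 6 months it is about 0.1 points or less under constant hazards. All of this is well inside a half-width of about 6 points.

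It would be too strong to say that the three proportions are overstated as a fact, since that depends on deaths the article does not quantify. Nor can the estimate be called the primary one, since no endpoint is labelled primary.

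**What to change.** In the Data Analysis Plan, state how death before AF detection is handled. Report the Aalen-Johansen cumulative incidence of first AF detection, with death before AF as a competing event and 95% CIs at 6, 12 and 24 months. Keep one minus Kaplan-Meier as a sensitivity analysis, labelled as detection in the absence of death. Leave the Cox models as they are and describe them as cause-specific.

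No change to the survey items is needed, because death is already recorded at each follow-up. The cost is a change of wording and one more routine. That routine may lie outside the single package the article names for all analyses (JMP version 13), in which case the software statement needs a matching edit. The headline proportion will be slightly lower.

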### Conclusions

By conducting this prospective LOOK multicenter study, the characteristics of patients with occult AF detected by ICMs will be clarified in more detail than previously reported by analyzing imaging studies on admission and during follow-up, serial measurements of blood markers, and various physiological findings. We hope that our findings will contribute to the identification of markers and enable the development of a risk scoring system with a new and better screening algorithm, which could inform future guidelines for stroke screening in patients with CS as well as the development of comprehensive clinical trials.

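### The ROC analysis has no time horizon, pre-specified marker or stated internal validation, so accuracy may be overstated for any marker or score selected in the same cohort

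*Protocol article*

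**What the plan says.** All of the statistical methods are in the Data Analysis Plan section of the protocol article.

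- **Detection over time:** "We will investigate the rate of initial AF detection within the initial 6, 12, and 24 months after ICM implantation using Kaplan-Meier survival estimates".
- **Predictors:** "Cox proportional hazards regression models will be fitted to various baseline characteristics for the prediction of AF".
- **Group tests:** the items of Textbox 2 are compared between patients with and without AF by chi-square or Wilcoxon rank-sum test, with Yates or Fisher where counts are small.
- **Accuracy:** "Receiver operating characteristic curve analysis will be performed to assess the predictive accuracy of a variable in AF detection".
- **Significance:** one threshold for everything, "with *P*<.05 indicating statistical significance".

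The Sample Size section gives the basis for enrolment: "we decided to enroll 200 patients in this observational study to perform statistical analyses, including multivariate regression analysis, with sufficient statistical power". The only AF rate there comes from a cited subanalysis, "including 221 patients with a 30% AF detection rate". The Results section reports that "213 patients have provided written informed consent in May 2021 and are currently in the follow-up phase".

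On intended use, the Conclusions section hopes that the findings will "enable the development of a risk scoring system with a new and better screening algorithm". The abstract's conclusion is firmer and speaks of generating such a score.

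**The concern.** Two separate matters meet in the ROC sentence.

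**Selection.** One cohort is described. The same patients would show which markers are associated with AF and would then supply the accuracy of those markers. An AUC taken on the data that picked the marker is on average higher than the AUC the marker would reach in new patients. The gap grows with the number of candidates and shrinks with the number of events. The study wants a score that helps decide who receives a monitor, so an overstated AUC could carry into later screening rules.

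**Label.** Kaplan-Meier and Cox treat first AF detection as a censored time. A plain ROC curve and the two-group tests need each patient to be AF or non-AF. Table 1 foresees withdrawal, non-attendance and death. For a patient who leaves at month 3 without AF, the plan does not say which group applies, or whether the ROC refers to 6, 12 or 24 months.

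**Working it through.** **1. The plan's own figures.** No AUC target is given. The figure of 200 cannot be reproduced, because the Sample Size section states no effect size, power, dropout or number of predictors. What follows from it:

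- Expected AF cases = N × detection rate = 200 × 0.30 = 60. For the 213 who consented, 213 × 0.30 = 63.9, about 64.

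**2. Number of candidates (not stated).** The plan says only that various baseline characteristics are modelled. Textbox 2 lists about 61 items: some 58 from patient characteristics to carotid ultrasound, plus the stroke severity scale, the cognitive test and the disability scale. That is a list of data to collect, not a list of predictors. I therefore use 10 to 60 as a range. For k independent null candidates, the chance of at least one result below .05 is 1 − 0.95^k:

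- k = 20: 1 − 0.95^20 = 0.64
- k = 40: 1 − 0.95^40 = 0.87

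**3. Size of the optimism.** Simulated cohorts had N = 200, 30% AF and independent normal markers. Either no marker is predictive, or three are, with a log odds ratio of 0.4 per SD. Optimism = mean apparent AUC − mean AUC in new patients.

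*One pre-specified marker (log odds ratio 0.5 per SD):* apparent 0.637, true 0.636. Optimism is essentially zero.

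*Best single marker out of k:*

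| k | 3 true: apparent / true | optimism | none true: apparent / true | optimism |
|---|---|---|---|---|
| 10 | 0.641 / 0.597 | 0.04 | 0.585 / 0.500 | 0.09 |
| 20 | 0.644 / 0.592 | 0.05 | 0.598 / 0.500 | 0.10 |
| 40 | 0.643 / 0.586 | 0.06 | 0.609 / 0.500 | 0.11 |
| 60 | 0.64 / 0.58 | 0.06 | 0.61 / 0.50 | 0.11 |

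*Score from all markers with univariable P<.05, combined in a logistic model:*

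| k | 3 true: apparent / new patients | optimism | none true: apparent / new patients | optimism |
|---|---|---|---|---|
| 10 | 0.682 / 0.635 | 0.05 | 0.619 / 0.500 | 0.12 |
| 20 | 0.694 / 0.625 | 0.07 | 0.621 / 0.499 | 0.12 |
| 40 | 0.716 / 0.615 | 0.10 | 0.649 / 0.500 | 0.15 |

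The score results count only simulated cohorts in which at least one marker passed the screen. A score drawn from all 60 items would do worse (0.73 against 0.61 with three true markers, 0.67 against 0.50 with none). That case needs every Textbox 2 item to be a candidate, so I leave it out of the stated range.

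For scale, the sampling SD of a single marker's AUC at this size is about 0.04. The optimism is at least that large, and always upward.

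**4. Effect of the undefined label.** The assumptions are 30% AF by 24 months, exponential dropout and a marker whose uncensored 24-month AUC is 0.739.

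| Dropout unrelated to marker | leavers counted as non-AF | leavers excluded |
|---|---|---|
| 10% | 0.735 | 0.739 |
| 20% | 0.732 | 0.740 |
| 30% | 0.729 | 0.741 |

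If 20% drop out and dropout depends on the marker, the change runs from about −0.03 to +0.01, depending on the direction of the dependence and on how leavers are handled.

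**The case against.** The strongest reply is that much of this rests on silence. The text is a journal article; a full protocol or analysis plan may fix the horizon, the handling of leavers and the validation. Nowhere does the article say that censoring will be ignored or that optimism will go uncorrected, and Kaplan-Meier and Cox show that censoring is understood. The ROC sentence concerns a single variable, and a variable named in advance carries no optimism. The screened logistic score in the working is not an analysis the article describes, since its prediction models are Cox. Early loss may also be limited: follow-up is fixed at 24 months, patients with a life expectancy within 2 years are excluded, and device data are transmitted remotely.

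Most of this stands, and it makes the point conditional. It does not remove it. The section is detailed enough to name the small-count correction and the software version, yet its ROC has neither a marker nor a horizon. The protection that a pre-specified marker would give is not available, because none is named. The best-of-k table shows that choosing one variable is enough to create optimism, without any combined score.

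A reader might also infer that leavers will be counted as AF-free and that this inflates the AUC. The article does not say so, and with dropout unrelated to the marker such counting lowers the AUC slightly.

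**Conclusion.** The point holds conditionally. If markers are selected or combined in this cohort and the AUC is reported uncorrected, it would be too high by roughly 0.04 to 0.10 when some markers are truly predictive, and by up to about 0.15 when none are. The range covers the best single marker out of 10 to 60 candidates and a score screened from 10 to 40. It rests on about 60 AF cases, independent markers and modest effects. The candidate numbers and effects are assumptions; the documents give neither. The case with no predictive marker is an extreme, since the Sample Size section cites studies that reported associations.

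The missing label for patients with incomplete follow-up is a separate and lesser defect. Its effect is probably a few hundredths at most, in either direction, under assumed dropout.

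It would go too far to conclude that reported accuracy will be inflated, or that the sponsor has chosen to ignore censoring and validation. The article supports only that these matters are not fixed where the ROC is specified.

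**What to change.** 1. Replace the ROC without a horizon by Harrell's C, or by a censoring-weighted AUC at 6, 12 and 24 months, the time points already used for Kaplan-Meier. This also settles how leavers enter.
2. Name in advance any marker whose accuracy is to be reported as it stands. For every selected marker and any combined score, report the optimism-corrected value from a bootstrap that repeats the whole selection step in each resample (for example 500 resamples), beside the apparent value.
3. Base inference on baseline markers on the Cox models already planned, and keep the AF versus no-AF comparisons descriptive.

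No new data or patients are needed. The cost is more analysis work, possibly other software than the package named, and a lower reported accuracy. The change should be settled before the data are analysed.
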